## 8. STATISTICAL METHODS

The statistical analysis will be described in the statistical analysis plan written by the Coordinating Investigator and checked by a biostatistician, which is binding and will be finalized before database lock or before any other analysis takes place.

### 8.1 Study hypotheses and hypothesis

To evaluate whether the intervention group has a larger improvement in the healthy lifestyle questionnaire score than the comparison group, the following hypotheses were formulated:

- Null hypothesis ( $H_0$ ): the score in the healthy lifestyle questionnaire is the same in the intervention and comparison group (or the intervention program does not improve the score of the questionnaire).
- Alternative hypothesis ( $H_1$ ): the score in the healthy lifestyle questionnaire is larger for the intervention group than the comparison group.

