## SYNOPSIS

|                                                   |                                                                                                                                                                                                                                                                                                                                                                                                                                                                                                                                                                                                                                                                          |
|---------------------------------------------------|--------------------------------------------------------------------------------------------------------------------------------------------------------------------------------------------------------------------------------------------------------------------------------------------------------------------------------------------------------------------------------------------------------------------------------------------------------------------------------------------------------------------------------------------------------------------------------------------------------------------------------------------------------------------------|
| HYPOTHESIS                                 | 
To evaluate whether the intervention group has a larger improvement in the healthy lifestyle questionnaire score than the comparison group, the following hypotheses were formulated:
 
 
- Null hypothesis (<math>H_0</math>): the score in the healthy lifestyle questionnaire is the same in the intervention and comparison group (or the intervention does not improve the score of the questionnaire).
 
- Alternative hypothesis (<math>H_1</math>): the score in the healthy lifestyle questionnaire is larger for the intervention group than the comparison group.
 
                                 |

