### 4.3 Sample size

The present study is based on a three-level hierarchical design where two groups of 3 healthcare centers (matched in population size and geographical area, urban/rural) will be randomized to the intervention and comparison group, and healthcare workers within the same cluster provide the intervention allocated to the participants

The sample size will be based on the expected differential change in the primary outcome of the study (healthy lifestyle score) determined by the questionnaire developed and validated in India by Dubasi and co-workers to assess the adherence to dietary and physical activity advice for weight control in lifestyle-related diseases. The questionnaire's total score ranges between 14-65 points, a lower score indicates poor adherence to a healthy lifestyle, while a higher score indicates good adherence.

In this cRCT, 1 group of 3 healthcare centers will be randomly allocated to the intervention group and the other group of 3 healthcare centers to the comparison group. A comparable study measuring also lifestyle behavior changes as primary outcome, and using a similar score scale has reported a differential improvement from baseline to follow-up after 35 weeks of 20% between intervention and comparison groups. Also, literature has reported intra-class correlation (ICC) coefficients for interventions concerning dietary and physical activity improvements range in between 0.007-0.3.

Based on this previous evidence and the demographics of our study setting, the following assumptions have been used to approximate a power calculation estimate. This calculation was done using STATA version 16 for a cluster-randomized design assuming a realistic number of participants sample from each healthcare center whereby the following parameters were considered:

- 48 participants per cluster (144 participants per intervention program)
- Improvement of 12% in the lifestyle questionnaire score between intervention and comparison group (+ 6 score points)
- Effect size of 0.7 (score of the average person in the experimental group is 0.7 standard deviations above the average person in the comparison group, thus surpasses the scores of 69% of the comparison group).
- ICC of 0.1
- 20% loss to follow up and no attrition expected

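### H1 is worded as a larger score although the question is a larger improvement, and section 8.3.3 names neither the tested contrast nor any adjustment for the baseline score

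*Combined protocol and SAP*

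**What the plan says.** The opening sentence of section 8.1 sets the aim as finding out "whether the intervention group has a larger improvement in the healthy lifestyle questionnaire score than the comparison group". The synopsis has the same sentence.

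The hypotheses that follow are put differently. H0 is that "the score in the healthy lifestyle questionnaire is the same in the intervention and comparison group", followed by a bracketed alternative, "or the intervention program does not improve the score of the questionnaire". H1 is that "the score in the healthy lifestyle questionnaire is larger for the intervention group than the comparison group". H1 mentions no baseline, change or visit.

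Section 4.3 uses both ideas. It says "The sample size will be based on the expected differential change in the primary outcome of the study (healthy lifestyle score" and so on, and it cites a comparable study's differential improvement from baseline. It then defines the effect size as a gap in level: "score of the average person in the experimental group is 0.7 standard deviations above the average person in the comparison group".

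Section 8.3.3 assesses the programme's impact from baseline to follow-up in the two groups, using a linear mixed model for repeated measurements with random cluster effects. It does not name a group-by-time term, a baseline covariate or a primary visit. Table 1 (section 5.1) schedules the score at baseline and at 6, 12, 18 and 24 months. Section 8.3.2 plans baseline tests between the groups but states no consequence for the model. Section 4.4 balances the two groups of three centres on population coverage and urban/rural area only.

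**The concern.** A comparison of levels and a comparison of changes respond differently to a gap between the arms that exists before the programme starts. The level comparison carries the lasting part of the gap into the estimated effect. The change comparison subtracts a stable gap. A baseline-adjusted comparison corrects for the gap in proportion to how well baseline predicts follow-up.

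With six centres this choice matters. The two groups are formed by hand and one random assignment decides which is treated, so the size of any centre gap is fixed before randomisation and only its direction is random. If the gap turns out large, the wording of H1, the wording of the aim and the unspecified model term could support different primary results. The analyst would then be choosing among them with the data in view.

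**Working it through.** **Inputs from the plan.** SD 7, ICC 0.1, target 6 points, 3 centres per arm, 48 enrolled and 40 analysed per centre, one-sided 0.05 (sections 4.3 and 8.4). The between-centre variance is 0.1 × 49 = 4.9 and the within-centre variance is 44.1. Normal approximations are used throughout, as they reproduce the plan's figures.

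**1. The plan's own power.** Design effect = 1 + 39 × 0.1 = 4.9. Effective size per arm = 120/4.9 = 24.5. SE = 7 × √(2/24.5) = 2.00. Power = Φ(6/2.00 − 1.645) = 0.912, against 91% stated. With one centre lost, SE = 7 × √(4.9/80 + 4.9/120) = 2.24 and power = 0.850, against 85% stated. The matching formula compares two score means at one time. It has no baseline term and no correlation over time.

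**2. Chance baseline gap between arms.** At 48 per centre, SD of the gap = √(2 × 49 × (1 + 47 × 0.1)/(3 × 48)) = 1.97 points. P(gap of at least 3 in either direction) = 2 × (1 − Φ(3/1.97)) = 0.13. P(at least 2) = 0.31. This treats the centres as draws from one distribution and ignores matching. If population size or urban/rural area predicts the score, the gap will be smaller.

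**3. A level comparison, given a gap.** It rejects above 1.645 × 2.00 = 3.29 points. Let r be the correlation of the arm difference over time (assumed; the documents give none). Given a baseline gap g, the follow-up difference has mean (effect + r·g) and SD 2.00 × √(1 − r²).

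| r | No effect, 3-point gap favouring intervention: P(reject) | True effect 6, 3-point gap against: power |
|---|---|---|
| 0.5 | 0.15 | 0.76 |
| 0.7 | 0.20 | 0.67 |
| 0.8 | 0.23 | 0.60 |

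The nominal values are 0.05 and 0.91. Averaged over gaps in both directions, the level comparison returns to 5%, because its SE contains the centre variance.

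**4. Precision of the three comparisons at 40 per centre.** Let V = 4.9 + 44.1/40 = 6.00 and C = rc × 4.9 + ri × 44.1/40. Here rc is the centre-level and ri the individual-level correlation between baseline and follow-up (both assumed; ri 0.4–0.7).

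- Level: √((2/3)V) = 2.00.
- Change: √((4/3)(V − C)).
- Adjusted, best slope on centre means: √((2/3)(V − C²/V)).
- Adjusted, slope equal to ri, which is closer to what an individual covariate gives: √((2/3)(V + ri²V − 2·ri·C)).

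| rc | ri | Change | Adjusted, best slope | Adjusted, slope ri |
|---|---|---|---|---|
| 0.5 | 0.4 | 2.04 | 1.75 | 1.76 |
| 0.5 | 0.7 | 1.93 | 1.69 | 1.72 |
| 0.8 | 0.4 | 1.48 | 1.37 | 1.52 |
| 0.8 | 0.7 | 1.32 | 1.25 | 1.26 |

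At rc 0.5, an unadjusted change gains little or nothing over the level, while adjustment does gain. At rc 0.8, change and adjustment are close, and in one cell change is marginally better.

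**5. Power for 6 points with a single r.** At r = 0.3, change has power 0.81 and baseline adjustment 0.93. At r = 0.5, they have 0.91 and 0.97.

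**The case against.** The strongest reply is that the plan already intends a comparison of change. The hypotheses are introduced by a sentence about improvement, the bracket in H0 mentions improvement, and section 8.3.3 spans baseline to follow-up. The natural reading of that model is a group-by-time contrast, in which a stable centre gap cancels. This stands. A reader might infer from H1 that the stated test is a level test, but the documents do not say so. What is missing is the name of the contrast.

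A reader might also suppose that the primary test is an arm term averaged over all five visits, so that a constant 6-point effect would shrink to 6 × 4/5 = 4.8. No section specifies such a term, so that dilution cannot be charged to the plan.

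Nor does the sample size simply contradict H1. Section 4.3 speaks of change, but its effect size and its reproducible power are on the level.

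Under randomisation the arms have equal expected baseline means, so level and change have the same expected treatment difference. This also stands. The issue is behaviour given a realised gap, and precision. It is not average bias or an inflated overall error rate.

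Finally, the introduction to section 8 leaves detail to an analysis plan to be finalised before database lock or any other analysis. That gives the sponsor a place to make the repair. It does not resolve the wording of H1.

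**Conclusion.** The point holds as a mismatch of wording together with an unnamed primary contrast and an unused covariate. It does not show that the planned test is wrong. On the plan's inputs, a baseline gap of at least half the 6-point target arises about 13% of the time before any benefit from matching. Given a 3-point gap, a level comparison would reject a true null with probability 0.15–0.23, or have power of 0.60–0.76 against the target effect, for assumed r of 0.5–0.8.

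Baseline adjustment improves on the level comparison in every case shown. It improves on unadjusted change clearly at a centre-level correlation of 0.5, and little or not at all at 0.8. It would be tempting to say that the baseline score removes most of the noise. With the best slope, the variance cut (C²/V²) is only 23–29% at 0.5 and reaches 53–61% at 0.8. The documents give no correlation to support the higher figure.

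These results rest on normal approximations, equal variances at baseline and follow-up, assumed correlations, and gaps that arise by chance. The separate consent forms for the two arms (section 5.2) suggest that allocation may be known at consent, in which case a gap need not be chance alone.

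**What to change.** In section 8.1 and the synopsis, word H0 as no difference between arms in change from baseline in the questionnaire score, and H1 as a larger change in the intervention arm.

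In section 8.3.3, estimate that difference from the follow-up visits with each woman's baseline score as a covariate, or fit all visits with baseline means constrained equal across arms. With the baseline score as covariate, modelling the follow-up score or the change gives the same arm estimate at a given visit, so the model matches the reworded hypotheses. Name this contrast as the primary test, and say which follow-up visit or average of visits it refers to.

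In sections 4.3 and 8.4, state that the power figures come from a comparison of score levels and give any correlation assumed for the adjusted analysis.

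The cost is text in these sections and the forthcoming analysis plan. No new data are needed, because the score is already scheduled at baseline for all participants.

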### 8.2 Variables of interest

After the termination of the study, the primary and secondary outcomes will be evaluated for normality by the Kolmogorov-Simonov test and visual inspection of histograms. In case of non-normally distributed outcomes, log transformation and non-parametric tests will be considered.

The primary outcome (healthy lifestyle questionnaire score) will be a variable with ordinal values ranging between 14-65 points. The secondary outcomes of anthropometrics (weight [kg], height [m], BMI [kg/m^2], waist circumference [cm]), clinical indicators (glycemia [mg/dL] and blood pressure [mmHg]), and total MET-min/week and kcal/week collected by the physical activity questionnaire will be variables with continuous values. Only the outcome of diet diversity will be provided as an ordinal variables ranging from 0-10.

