| FOLLOW-UP                         | Participants will be followed up for 24 months and measurements will be assessed every 6-months period (total of 5-time points: baseline + 4 follow up visits).                                                                                                                                                                                                                                                                                                                                                                                                                                                                                                                                                                                                                 |
| ANALYTICAL METHODS                | Not applicable.                                                                                                                                                                                                                                                                                                                                                                                                                                                                                                                                                                                                                                                                                                                                                                 |
| SAFETY                            | This study imposes a low risk for the participants as the intervention program comprises a lifestyle modification through education and motivational strategies and the measurements to be taken are non-invasive, with the exception of blood glucose assess by blood sampling using a finger prick. For this measurement, guidelines with all the necessary steps and equipment will be followed.                                                                                                                                                                                                                                                                                                                                                                             |

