### 8.3 Statistical methods

#### 8.3.1 Analysis populations

The analyses will be conducted based on the intention-to-treat principle. A probability of <0.05 will be considered statistically significant for all tests. All analyses will be conducted using STATA (Release 16/SE. College Station, TX: StataCorp LP) by ITM's staff.

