#### 8.3.3 Primary analysis

After the termination of the study, the primary and secondary outcomes will be evaluated for normality by the Kolmogorov-Simonov test and visual inspection of histograms. For the primary ordinal outcome (Healthy lifestyle Questionnaire Score), the impact of the intervention program

between baseline and follow up of the 2 groups (intervention and comparison group) will be assessed by using random effect (clusters) linear mixed models for repeated measurements.

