On average conditions, meaning 30 participants per cluster, change of 12%, ICC of 0.1 and SD of 7 points, a power of 89% would be reached. However, if one cluster withdrawal the power would decrease to 82%, borderline to detect a change with enough power. Hence, to ensure power considering a withdrawal of 1 cluster, sample size calculation presented in section 4.3 entails 40 participants per cluster plus 20% loss to follow, indicating 144 participants per arm (total of 288 participants enrolled in the study) are needed to detect a change of 12% (with ICC 0.1 and SD of 7) between the intervention and comparison group with a level of significance of 95%.

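### Normality is checked on the raw outcomes instead of the model residuals, and the result can reopen the choice of primary analysis after the data are seen

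*Combined protocol and SAP*

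**What the plan says.** Section 8.2 states that "the primary and secondary outcomes will be evaluated for normality by the Kolmogorov-Simonov test and visual inspection of histograms". It continues: "In case of non-normally distributed outcomes, log transformation and non-parametric tests will be considered". Both sentences cover the primary and secondary outcomes together. The primary score "will be a variable with ordinal values ranging between 14-65 points".

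Section 8.3.3 repeats the normality check and then says the effect on the primary score "will be assessed by using random effect (clusters) linear mixed models for repeated measurements". It does not repeat the fallback. The Synopsis follows the same pattern. Section 8.3.6 relies on the mixed model and maximum likelihood to deal with missing values.

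Section 8.3.1 adds a general threshold: "A probability of <0.05 will be considered statistically significant for all tests". Section 8 promises a separate, binding SAP before database lock.

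The plan does not say:
- whether visits, arms or centres are pooled for the normality check;
- whether the test is corrected for an estimated mean and SD;
- how the test and the histogram are weighed against each other;
- which non-parametric test is meant;
- that model residuals will be examined.

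**The concern.** The check looks at the wrong quantity. A linear mixed model assumes roughly normal errors and random effects. The raw scores mix arms, visits, centres and women, so their distribution does not answer that question.

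The Kolmogorov–Smirnov test also suits these data poorly. Its reference distribution is for independent draws from a continuous distribution with known parameters. The primary score is a sum of whole-number item weights (Annex 6). It is measured repeatedly on the same women within six centres, and its mean and SD would be estimated from the same data.

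What is at stake is the primary analysis. A finding of non-normality lets the analyst consider another method after seeing the data, in a trial that section 4.4 says is not blinded. A log scale or a rank test would no longer estimate the points difference behind the 6-point sample-size case. An ordinary rank test would also ignore clustering and drop the repeated-measures likelihood that section 8.3.6 relies on for missing data.

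**Working it through.** **Inputs from the documents.** Six centres with 48 women enrolled in each (288 in total). The sample size "entails 40 participants per cluster plus 20% loss to follow". Visits: "total of 5-time points: baseline + 4 follow up visits". Base case SD 7 and ICC 0.1, SD range 5 to 9, effect +6 points (sections 4.3 and 8.4). Level 0.05 (section 8.3.1). Pooled values: 288 × 5 = 1,440 with no loss, or 240 × 5 = 1,200 at 40 per centre.

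**Assumptions not in the documents.** Score mean 38. Within-woman correlation 0.3 to 0.7 (share of the non-centre variance). Effect constant after baseline. Pooling of visits. Test version: uncorrected, or corrected for estimated parameters (Lilliefors).

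**Step 1: the plan's own figure.** The plan gives no rejection rate for the normality test. Its base case can be confirmed through the stated 91% power. Design effect 1 + 39 × 0.1 = 4.9. SE = √(2 × 49 × 4.9 / 120) = 2.00. Power = Φ(6/2.00 − 1.645) = Φ(1.355) = 0.912. The inputs are therefore read correctly.

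**Step 2: why whole numbers matter.** The distribution of a rounded normal score rises in steps. The largest step is about 0.3989/SD, so the empirical curve sits about half a step from the fitted normal curve even when the underlying values are normal:

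- SD 5: 0.3989/10 = 0.0399
- SD 7: 0.3989/14 = 0.0285
- SD 9: 0.3989/18 = 0.0222

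The 5% critical distances of the uncorrected test are 0.0357 (n = 1,440) and 0.0391 (n = 1,200). At one visit (n = 288) the distance is about 0.0357 × √5 = 0.080. The Lilliefors values are 0.0239 (n = 1,440) and 0.0260 (n = 1,200).

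With visits pooled, the rounding gap alone exceeds the uncorrected limit at SD 5. It comes within sampling noise of the limit at SD 7 and falls further short at SD 9. At one visit it is far below the limit at every SD.

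**Step 3: simulation.** Score = 38 + centre effect + woman effect + 6 (intervention arm, after baseline) + error, all normal, rounded and limited to 14–65. There were 1,500 to 2,000 trials per setting. Share of trials in which the test rejects, with visits pooled and the test uncorrected:

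| SD | Effect | Women per centre | Rejected |
|---|---|---|---|
| 7 | none | 48 | 83–87% |
| 7 | +6 | 48 | 73–80% |
| 7 | +6 | 40 | 56–65% |
| 5 | +6 | 40 or 48 | 99–100% |
| 9 | +6 | 48 | 38% |
| 9 | +6 | 40 | 24% |

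Comparisons:

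- One visit, SD 7, uncorrected: about 1–3%.
- The same pooled data left unrounded (SD 7), uncorrected: 0–0.4%.
- Residuals (woman means and centre-by-visit means removed) from the rounded data at SD 7, uncorrected: 0–0.1%.
- Lilliefors version: about 100% pooled at every SD, and 40–59% at one visit with SD 7.

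At SD 7, then, the same kind of data give anything from about 1% to about 100%, according to pooling and test version. A log transform keeps the same ties, so it cannot remove this cause.

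**Step 4: an ordinary rank test.** Take a Mann–Whitney test at one visit, three centres against three, ICC 0.1, no effect. Ignoring clustering inflates the variance by the design effect, so the true two-sided size is about 2[1 − Φ(1.96/√DE)]:

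- 40 per centre: DE 4.9, 1.96/2.214 = 0.885, size 0.38.
- 48 per centre: DE 5.7, 1.96/2.387 = 0.821, size 0.41.

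Simulation gives 36–41%, against a nominal 5%.

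**The case against.** The strongest reply is that the plan describes no automatic rule. The test is paired with histograms, and a rounded normal score with SD 7 would probably look normal in one. Alternatives are only to be considered. The mixed model is named for the primary score in the Synopsis, 8.3.3 and 8.3.6 without a fallback. The fallback sentence in 8.2 covers all outcomes, including glycemia and MET-minutes, where a transformation may be reasonable. A log-transformed score could stay in the mixed model and keep the repeated visits and the likelihood handling of missing data. The SAP still to come could settle the matter.

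Much of this stands. It rules out two stronger readings that a reader might infer:

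- *That normality would be wrongly rejected about 84% of the time.* That figure needs all five visits pooled, SD 7, no treatment effect, no loss to follow-up and the uncorrected test. The plan does not say that visits are pooled or which test version is meant, and it expects both an effect and 20% loss. Tested visit by visit with the uncorrected test, rounding is rarely a cause of rejection.
- *That the primary analysis would then change, with a false-positive rate near 40%.* The chance of an actual switch was not estimated and cannot be from the documents. The 36–41% applies only if an ordinary unclustered rank test were chosen, and the plan names no test.

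What the reply does not remove is the open discretion. The wording in 8.2 reaches the primary score, sets no criterion, and is applied after the data are known.

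**Conclusion.** The point holds in a limited form. The plan checks raw outcomes where the model's assumption concerns residuals and random effects, and it leaves an undefined, post-data route away from the primary model. With visits pooled, the Kolmogorov–Smirnov result says little about model adequacy for this integer score: about 24–100% rejection across the plan's SD range, against under 1% for the same data unrounded or for residuals (both checked at SD 7). At one visit the uncorrected figure is about 1–3% (SD 7).

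These rates rest on the assumed score mean, within-woman correlation, pooling and test version. They describe the preliminary test only, not the trial's type I error or power. The harm depends on which alternative is taken. It is modest for a log scale inside the mixed model and serious for a rank test that ignores the six centres.

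**What to change.** In sections 8.2 and 8.3.3, and in the SAP to come:

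1. Remove the Kolmogorov–Smirnov test of raw outcomes as a basis for choosing the analysis.
2. State that the linear mixed model on the untransformed score is the primary analysis whatever the distribution of the raw score.
3. Check assumptions with plots of the model residuals.
4. Label any transformed or rank-based analysis of the primary score as sensitivity only, and require any rank-based method to respect clustering by centre.

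The Synopsis needs the matching edit. The cost is a few sentences and no new data. The small downside is that the primary model is kept under mild non-normality, which the sensitivity analysis would show.
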